## Methods

### Design

This is a multi-centre, randomised controlled, interviewer-blinded trial, with four parallel groups, 1:1:1:1 allocation ratio. Potential participants will be identified by collaborating professionals at recruitment sites and those interested in participating will sign an informed consent form. Subsequently, those selected based on inclusion/exclusion criteria (*n* = 400) will undergo preliminary testing and will be randomly allocated to one of the four study groups. In this study, there are three intervention groups and one group receiving TAU. Intervention groups are: (1) cognitive rehabilitation with the GRADIOR programme (GRA), (2) a computer-based psychosocial stimulation group (ehcoBUTLER) (PSS) and (3) a group receiving a combined treatment of GRADIOR together with computer-based psychosocial stimulation (ehcoBUTLER CARE) (COM). Primary and secondary measures data will be collected at baseline, at 4 months after the start of the treatment and at 12 months, immediately after completing the interventions. Follow-up assessments will be carried out 4 and 12 months after finishing the treatment (months 16 and 24 of the study). A preliminary study of usability will be conducted before the start of the trial. The full study timeline is described in Table 2.

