### Sample size

Maximal sample size for the study was set at 400 participants with dementia and MCI. We considered a 15% dropout by participants during the 12 months of interventions and 12 months of follow-up. Therefore, the final sample size for the study is likely to be 340 participants.

Considering that the standard deviation of the selected population in the selected variables of the study was unknown and the population size was undetermined, we opted for a calculation of the sample size for an infinite population with the maximal level of variability of the dependent variables of the study (*p* = *q* = .5). If the population scattering parameters are unknown, this calculation allows for a more conservative sample size, meaning the biggest sample size [30].

The calculation was executed using the following equation (α = .05):$$ n=\frac{Z_{\raisebox{1ex}{$\propto $}\!\left/ \!\raisebox{-1ex}{$2$}\right.}^2\ast {0.5}^2}{e^2}, $$

where 0.52 is a maximal variability (*p* * (1 − *p*)), *Z*_∞/2_ corresponds to scores in the percentile *α*/2 (.025) of a normal distribution, and *e* corresponds to the error acquired for the desired sample size, with a result of *e* = 5.3% for a sample size of 340 participants.

On the other hand, based on the Friedman table for determining effect size [31], for the primary outcome measure ADASCog to achieve 80% power (alpha 0.05) on a sample of 340 participants we are looking for an approximate effect size of 0.30, which is similar to a separate study protocol on cognitive rehabilitation in PwD [9].

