### Outcome measures and hypotheses

#### Primary outcome measures

GRADIOR stimulates cognitive functioning, which is reflected in changes in separate cognitive domains. Outcome measures were selected accordingly. The primary aim of the study is to determine whether the cognitive rehabilitation programme GRADIOR improves cognition of people with MCI and PwD in a specific (GRA) or combined treatment group (COM). Based on previous research in this area, and our previous experience with the GRADIOR programme in a clinical setting, we expect that the two treatment groups using GRADIOR solely and in combination (COM) will achieve significantly higher scores in cognitive testing than the TAU group after 4 and 12 months of treatment. The primary outcome measure will be an ADASCog Cognitive Subscale [36].

The change in cognitive performance after a period of 4 months and 12 months in comparison with baseline results will be measured in all study groups using the *ADASCog Cognitive Subscale* [36] as the primary outcome, which evaluates cognitive performance in memory, praxis, orientation and language. Additionally, the Spanish version of the *Mini-Mental State Examination (MMSE)*, consisting of 35 questions [37], will be used*.* For a more comprehensive evaluation of a participant’s cognitive profile, we will use a variety of tests: the *Clock Drawing Test* [38] for general cognitive and spatial functioning, *WAIS III – Coding digit symbol, Calculus and Digit Span* subtests [39] to evaluate processing speed, numeric reasoning and working memory respectively, the *Rivermead pattern recognition test* [40] for visual memory, *Trail-making tests A and B* [41] to monitor motor functioning, executive functioning and visual-spatial abilities (part A) and also sustained attention (part B), the *Cambridge Cognitive Examination (CAMCog) – matrices* subtest [42] to examine intellectual ability, analogic reasoning and abstraction capacity and *Semantic and phonologic verbal fluency* [43] and [44] on animal category and letters P, M and R.

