## Discussion

We will conduct a RCT with a long-term cognitive rehabilitation intervention and follow-up. This innovative RCT aims to determine the influence of a long-term, computerised, cognitive rehabilitation programme on people with MCI and PwD in comparison to psychosocial stimulation and TAU. The preliminary usability study will focus on ensuring that this type of treatment is more convenient and beneficial for older people, as well as for healthcare professionals.

Limitations of the study are related to the long duration of the treatment along with the 1 year follow-up. Therefore, we expect a large number of participants to drop out due to loss of interest, medical reasons or worsening of a related health condition, changes in life situation, etc. This potential dropout rate has been considered in the sample size calculation to ensure the success of the trial. We also foresee the potential for interviewers and staff to drop out during the study. In this case, every new member of staff recruited will be informed about the study and every new interviewer will undergo the same training in evaluation tools as those recruited at the start of the study.

For ethical and practical reasons, participants in this study will not be blinded to the intervention condition. Huntley et al. [55] recommend conducting single-blinded psychosocial intervention RCTs to minimise other factors, such as socialisation, when using the TAU control group (e.g. patient blinded and assessor blinded, but not therapist blinded). However, this is difficult to apply in practice due to ethical reasons. Therefore, we are conducting a single-blinded RCT with four parallel groups. In this study, all interviewers will be blinded to participants’ treatment allocation. Study coordinators who will manage and adjust the GRADIOR treatments of all participants will do so only based on data obtained from the programme and manage this under a participant’s code (Fig. 1 and Additional file 1).

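### The claimed 80% power for an effect size of 0.30 needs 170 against 170; the planned comparisons have 85 against 85 and about 49% power

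*Protocol article*

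**What the plan says.** The Sample size section sets a maximum of 400 participants, allows 15% dropout over the 12 months of intervention and 12 of follow-up, and arrives at 340. It supports that number in two ways.

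- **Precision formula.** Because the standard deviations were unknown, "we opted for a calculation of the sample size for an infinite population with the maximal level of variability of the dependent variables", taking p = q = 0.5. This gives an error of 5.3% at 340.
- **Power statement.** For ADASCog, "to achieve 80% power (alpha 0.05) on a sample of 340 participants we are looking for an approximate effect size of 0.30". The source is a published effect-size table. The metric is not named, and nothing is said about the number per arm.

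The Design section describes a trial "with four parallel groups, 1:1:1:1 allocation ratio". Under Primary outcome measures, the two groups using GRADIOR (alone, GRA, and combined, COM) "will achieve significantly higher scores in cognitive testing than the TAU group after 4 and 12 months of treatment". The Analysis section plans repeated measures ANOVA over baseline, 4 and 12 months, with Bonferroni or Dunnett corrections post hoc if needed. The Discussion adds that "we expect a large number of participants to drop out".

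**The concern.** The power statement attaches 0.30 to the whole sample of 340, but no primary comparison uses all 340. Each sets one active arm against treatment as usual (TAU), which is half of the completers. If 0.30 is a standardised mean difference, the trial would miss a true effect of the size it seeks about half the time in each contrast, while its readers are told one time in five. A null result for GRADIOR could then be taken as evidence of no effect when the comparison was too small to show one. The precision formula does not fill the gap, because it involves neither power nor a difference between groups.

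**Working it through.** **Inputs from the protocol article.** 400 randomised, 15% dropout, alpha 0.05, power 80%, effect size 0.30 (Sample size); four arms at 1:1:1:1 (Design); GRA against TAU and COM against TAU on ADASCog (Primary outcome measures). The power sentence does not say whether the test is one- or two-sided. Two-sided is taken here, as the precision formula in the same section uses the α/2 percentile.

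**Numbers per arm.** 400 × 0.85 = 340, and 340 / 4 = 85.

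**Reproducing the plan's figures.**

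- Precision: e = 1.96 × 0.5 / √340 = 0.053. The 5.3% reproduces, as the half-width of a 95% confidence interval for one proportion.
- Power: for two groups of n each, power ≈ Φ(d√(n/2) − 1.96). With n = 170 and d = 0.30, 0.30 × √85 = 2.766, and Φ(0.806) = 79.0% (noncentral t: 78.8%). The detectable d at 80% power is 0.305. So the statement reproduces for 170 against 170.

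**Other readings of 0.30 at a total of 340.**

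| Reading | Power at 0.30 | Value detectable at 80% |
|---|---|---|
| Cohen's f, four-group ANOVA | 99.8% | 0.18 |
| Correlation | above 99.9% | 0.15 |
| d, one-sided, 170 against 170 | 86.9% | – |

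None of these gives 80%.

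**The planned contrasts, 85 against 85.** 0.30 × √42.5 = 1.956, and Φ(1.956 − 1.960) = 49.8% (noncentral t: 49.4%). The detectable d is about (1.960 + 0.842) × √(2/85) = 0.43.

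| Handling of multiplicity | Power at d = 0.30 | Detectable d at 80% |
|---|---|---|
| None | 49% | 0.43 |
| Dunnett, two arms against TAU (critical value about 2.21) | 40% | 0.47 |
| Bonferroni, two contrasts | 38% | 0.48 |
| Bonferroni, six pairs | 24% | 0.54 |

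**Sensitivity.**

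- No dropout at all (100 against 100): power 56%.
- GRA and COM pooled against TAU (170 against 85): power 61%.
- Dropout of 25% to 35% (75 to 65 per arm, an assumed range): detectable d 0.46 to 0.50, unadjusted for multiplicity.
- For 80% power at d = 0.30, about 176 analysed per arm would be needed.

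**Baseline adjustment.** With a baseline-to-outcome correlation ρ, the residual SD shrinks by √(1 − ρ²). The article gives no ρ, so these values are assumptions (85 against 85, no multiplicity correction):

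| ρ | Power at d = 0.30 | Detectable d at 80% |
|---|---|---|
| 0.5 | 62% | 0.37 |
| 0.7 | 78% | 0.31 |
| 0.8 | 90% | 0.26 |

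Bringing 0.432 down to 0.30 needs ρ = √(1 − (0.30/0.432)²) = 0.72. With Dunnett for two contrasts it needs √(1 − (0.30/0.469)²) = 0.77.

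**The case against.** **The metric is inferred.** The article never says that 0.30 is a standardised mean difference, and the table it cites is not at hand. As a correlation, 0.30 needs a total of only 85 for 80% power, which happens to equal one arm, and an 85-against-85 comparison would have about 98% power for it. The trial would then not be underpowered for its target. This limits the conclusion: 49% is conditional on d. It does not rescue the sentence, which ties 80% to 340; under f or r, power at 340 would be close to 100%.

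**A 170-against-170 contrast exists inside the design.** GRA and COM together against psychosocial stimulation and TAU together would have 79% power, and the secondary aim concerns the interaction of the two components. But the primary hypothesis names TAU as comparator, and GRADIOR is scheduled three to four times a week in GRA and twice a week in COM, so the margin would average over two schedules.

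**The planned analysis uses the baseline.** The 49% is for a single time point without baseline adjustment, and the true figure may be higher. That stands, but the Sample size section claims no such gain and states no correlation.

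**Dropout.** The 15% covers 24 months, so more than 85 per arm may remain at 4 and 12 months, and the Discussion says dropout was allowed for. With nobody lost, power is still only 56%.

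**Conclusion.** The power statement is wrong for this design. Read as a standardised mean difference, the only reading tested that gives 80% at 340, it holds for 170 against 170 and not for the planned 85 against 85. There, power is about 49% and the detectable difference 0.43 SD, or 40% and 0.47 SD with Dunnett for two contrasts. These figures assume two-sided 5% tests, 15% dropout spread evenly over the arms, one time point and no use of the baseline score. Using the baseline could recover much of the loss, but only with a correlation that the article does not state. The single-proportion formula reproduces and is irrelevant to a difference in mean ADASCog, so the section contains no valid calculation for its primary comparisons. Since this is the power claim for the primary outcome, it must be corrected.

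**What to change.** Rewrite the Sample size section:

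1. Delete the single-proportion calculation.
2. State that the effect size is a standardised mean difference (or whichever metric was meant), that the primary contrasts are GRA against TAU and COM against TAU, and that 85 per arm are expected to be analysed.
3. Give the detectable difference at 80% power for each contrast: about 0.43 SD without multiplicity correction and about 0.47 SD with Dunnett for two contrasts.
4. If 0.30 is kept as the target, say that it depends on a baseline-adjusted analysis and justify the assumed correlation: about 0.72 for one contrast at alpha 0.05, about 0.77 with Dunnett for two.

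The cost is a rewording and a less favourable stated detectable effect. Recruitment and conduct of the trial do not change.

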### Analysis

Statistical analysis will be conducted using programme IBM SPSS v.23. A descriptive analysis of demographic and personal data will be conducted and results will be compared between all groups. Firstly, an analysis of normality and homogeneity of the data will be conducted. For normally distributed data, the repeated measures analysis of variance (ANOVA) will be used to examine the hypotheses in inter-subject and intra-subject analysis as well as in their interaction. This will be applied to all outcome measures in a comparative analysis of the data collected at from baseline, after 4 months and 12 months of the treatment. In case of non-homogeneous data, non-parametric methods will be used for analysis (Mann–Whitney *U* test, Kruskal-Wallis analysis of variance, Wilcoxon signed-rank test, calculation of Spearman’s correlation coefficient, etc.). Bonferroni/Dunnet corrections will be applied during post-hoc analysis if needed. The possible effects of randomisation bias will be analysed using linear-mixed models including within-group and between-group factors. The significance level will be set at *α* = .05.

Effect sizes and their respective standard errors (SE) and confidence intervals will be estimated as Standardised Mean Change Index (dMR) for within-group comparisons, and as Standardised Mean Index difference (dC) for between-group comparisons, and corrected for small sample sizes [54]:

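### The 80% power stated for an effect size of 0.30 on 340 participants matches two groups of 170, not the four arms of about 85 in which each GRADIOR arm is compared with TAU

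*Protocol article*

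**What the plan says.** The Sample size section sets a maximum of 400 participants and allows for 15% dropout, leaving 340. It then gives two separate justifications. The first is a precision formula for a single proportion, with an error of 5.3% at 340. The second is the only power statement in the document: "to achieve 80% power (alpha 0.05) on a sample of 340 participants we are looking for an approximate effect size of 0.30". It refers to a published effect-size table and to a comparable trial protocol.

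The Design section describes a trial "with four parallel groups, 1:1:1:1 allocation ratio". The Primary outcome measures section expects that the two groups using GRADIOR (GRA and COM) "will achieve significantly higher scores in cognitive testing than the TAU group" at 4 and at 12 months, with ADASCog as the primary outcome. The Analysis section plans a repeated measures ANOVA over baseline, 4 and 12 months. On multiplicity it says that "Bonferroni/Dunnet corrections will be applied during post-hoc analysis if needed".

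**The concern.** The power statement uses the total sample, while the hypothesis concerns differences between single arms. Under equal allocation, a comparison of one GRADIOR arm with TAU uses only half of the 340. If 0.30 is a standardised mean difference, the stated power belongs to a comparison twice as large as the one named in the primary hypothesis.

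The precision calculation cannot fill the gap, because it concerns one proportion in one sample and says nothing about a difference in ADASCog between arms. The 80% statement is thus the only support for the sample size as a comparative trial. A reader who relies on it will expect the trial to detect 0.30 against TAU with 80% probability, and may give a non-significant result more weight than the design can bear.

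**Working it through.** **Inputs.** From Sample size: 400 randomised, 15% loss, alpha 0.05, 80% power, effect size 0.30. From Design: four arms, equal allocation. From Primary outcome measures: GRA and COM against TAU. The power statement does not give sidedness. I take two-sided, because the precision formula in the same section "corresponds to scores in the percentile *α*/2 (.025) of a normal distribution". The metric is not given either.

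**Numbers.** 400 × 0.85 = 340; 340 / 4 = 85 per arm.

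**Formula.** For two groups, the noncentrality is d × √(n₁n₂/(n₁+n₂)), and power comes from the noncentral t distribution on n₁+n₂−2 degrees of freedom.

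**Reproducing the plan's figure.** With 170 v 170, the noncentrality is 0.30 × √85 = 2.766 and the critical value 1.967. Power is 78.8%, and 80% is reached at d = 0.305. This agrees with the stated approximate 0.30.

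**The same calculation for the trial's contrasts, d = 0.30, one time point, no adjustment:**

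| Contrast | n | Alpha (two-sided) | Power at 0.30 | d for 80% power |
|---|---|---|---|---|
| GRA v TAU, or COM v TAU | 85 v 85 | 0.05 | 49.4% | 0.43 |
| Same, split over two comparisons | 85 v 85 | 0.025 | 38.2% | 0.48 |
| GRA+COM v TAU | 170 v 85 | 0.05 | 61.4% | 0.37 |
| GRA+COM v PSS+TAU (factorial) | 170 v 170 | 0.05 | 78.8% | 0.305 |

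For the first row the noncentrality is 0.30 × √42.5 = 1.956 against a critical value of 1.974, hence close to an even chance. If all 400 were retained (100 per arm), power would be 56%.

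**Other readings of the unlabelled 0.30.** On 340 participants, Cohen's f = 0.30 over four arms gives 99.8% power (80% needs f = 0.18), and a correlation of 0.30 gives more than 99.9%. At n = 85, a within-arm standardised change of 0.30 gives 78.1%, and a correlation of 0.30 gives 80.0%.

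**Effect of baseline and repeated measurements.** The protocol gives no correlation, so r is an assumption here. At 85 per arm, 80% power for 0.30 requires the variance to fall to (0.30/0.432)² = 0.482 of its unadjusted value.

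- *One follow-up, ANCOVA:* the factor is 1 − r². Power is 61% at r = 0.5, 78% at 0.7 and 90% at 0.8; 80% needs r of about 0.72.
- *Both follow-ups averaged, baseline-adjusted, equal correlations, constant effect:* the factor is (1+r)/2 − r². Power is 79% at r = 0.5, 83% at 0.6 and 90% at 0.7; 80% needs r of about 0.53. The factor is largest at r = 0.25 (0.625 − 0.0625 = 0.5625), where power is 74%.
- *Mean change from baseline, same assumptions:* the factor is 1.5 − 1.5r; 80% needs r of about 0.68.

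**The case against.** Four points can be made for the plan.

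**The metric is an inference.** The document does not say that 0.30 is a between-group difference, and the cited table is not available. Two readings at the true arm size also come out near 80%: a within-arm change and a correlation, each at n = 85. The Analysis section does name a within-group index. This stands as a caution against saying how the figure arose. It does not rescue the claim: the power is stated "to achieve 80% power (alpha 0.05) on a sample of 340 participants", not 85, and neither reading gives 80% for a difference between a GRADIOR arm and TAU.

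**The trial does contain a 170 v 170 contrast.** The four arms form GRADIOR yes/no by ehcoBUTLER yes/no. The Background hypothesis mentions other treatment groups as comparators as well as TAU, and the interaction is a secondary aim. GRA+COM against PSS+TAU has about 79% power. This stands as arithmetic, but the Primary outcome measures section names TAU as comparator, and the power statement invokes no factorial analysis.

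**The planned analysis is not a single-time-point t test.** This stands, and it is why 49% must carry its conditions. A reader might infer that the trial as planned has 49% power. The documents do not support that: power under repeated measures depends on an unstated correlation and on the contrast drawn from the model, and it could be well above 49%. Equally, the power statement claims no such gain.

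**Dropout and multiplicity are addressed.** The Discussion says that "we expect a large number of participants to drop out", but adds that the sample size allows for it, so the 15% is kept here. Post-hoc corrections are planned where needed; the power statement does not include them, and applying them would lower power.

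**Conclusion.** The power statement is wrong as written for the contrast that the protocol names. It gives 80% power for 0.30 without metric, contrast or arm size. As a standardised mean difference between groups, the figure matches 170 v 170, whereas a comparison of GRA or COM with TAU has about 85 v 85. On that comparison, power for 0.30 is about 49% and the detectable effect is 0.43; at 2.5% for two comparisons, 38% and 0.48. Pooling both GRADIOR arms against TAU gives 61%.

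These figures assume 15% loss spread evenly over the arms and an unadjusted two-sided test at one time point. They measure the gap in the stated justification, not the power of the final analysis. Two stronger conclusions might be drawn and are not supported: that the four arms were simply overlooked, since the origin of 0.30 cannot be seen, and that 0.30 is out of reach, since the factorial contrast comes close to 80% and a baseline-adjusted analysis could reach it at a sufficient correlation.

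**What to change.** Restate the last paragraph of the Sample size section with metric, contrast, number per arm, sidedness and alpha. Suggested wording:

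> With about 85 participants per arm, an unadjusted two-sided 5% comparison of a GRADIOR arm with TAU on ADASCog at one time point has 80% power for a standardised mean difference of 0.43 (0.48 at 2.5% for two comparisons), and 49% (38%) power for 0.30.

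If 0.30 with 80% power is to stay, state what delivers it: either the factorial main effect of GRADIOR, named as the primary contrast, or a baseline-adjusted model with the assumed correlation, the follow-ups it combines and the source of that correlation.

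The change costs one paragraph and needs no extra participants. The price is a less favourable stated detectable effect, or a commitment to a named contrast or model.
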